|                                                    | 
infusions, that represent the expected standard treatment should be administered.
 
The allocation of each patient in any given center to an active treatment or placebo will strictly follow a central randomization scheme. Clinical supplies allocation to centers should provide the necessary material so that any eligible patient can receive the assigned treatment. An IxRS will be used to manage randomization and drug shipment. The whole process will be handled in a manner that is blinded for the treatment received to all involved study personnel. The study period will be of a maximum of 40 days per patient. Patients will be closely monitored during the first 7 days following randomization with complete evaluations being performed at 24 hrs, 48 hrs, 72 hrs, then on Days 4 (96 hrs), 5 (120 hrs), 7 (+/-1 day), 14 (+/-2 days), 20 (+/-2 days), 40 (+/-3 days). Should a patient being discharged before Day 40, distant consultations by telemedicine may be undertaken if it is not deemed desirable that the patient comes back to the institution.
                                                                                                                                                                                                                                                                                                                                                                                          |

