## 4. STUDY DESCRIPTION

### 4.1 STUDY DESIGN

A randomized, double blind, multicenter, placebo- controlled, parallel group, fixed dose, phase II study. The study evaluates the efficacy and safety of glenzocimab. Patients will be screened for eligibility and all tests should have results prior to any randomization, so as to avoid screening failures to a maximum extent. The turn-around time for these tests should be comprised within 24hrs to allow for early inclusions if needed. Eligible patients (n=68) will be randomized in a 1:1 ratio to glenzocimab or placebo. Patient inclusions will be fractioned into sequential (3-day apart) cohorts of growing size (2, 4 then 6 patients), each balanced between glenzocimab and placebo in order to check safety in a gradual manner.

Glenzocimab will be administered by IV infusion. The dosing regimen will be 1000mg over 6 hrs, every 24 hrs for 3 consecutive days. All patients will receive in parallel the best medical care at the discretion of the investigating center, or per local guidelines. Unless, patient's condition worsens after the first infusion and/or an untoward adverse drug reaction precludes it, the treatment should be readministered 24 hrs after the initiation of the first infusion, and likewise after the second infusion, so that a total of 3 subsequent infusions, that represent the expected standard treatment should be administered. The allocation of each patient in any given center to an active treatment or placebo will strictly follow a central randomization scheme. Clinical supplies allocation to centers should provide the necessary material so that any eligible patient can receive the assigned treatment. An IxRS will be used to manage randomization and drug shipment. The whole process will be handled in a manner that is blinded for the treatment received to all involved study personnel. The study period will be of a maximum of 40 days per patient. Patients will be closely monitored during the first 7 days following randomization with complete evaluations being performed at 24 hrs, 48 hrs, 72 hrs, then on Days 4 (96 hrs), 5 (120 hrs), and 7 (+/-1 day), 14 (+/-2 days), 20 (+/-2 days), 40 (+/-3 days). Should a patient being discharged before Day 40, a distant consultation should be undertaken if it is not deemed desirable that the patient comes back to the institution.

STUDY PROTOCOL

ACT-CS-006-GARDEN-V6.0 FINAL

[figure not shown]

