## 4.2 STUDY DURATION FOR THE PATIENT

For each given patient, schedule will include:

- A screening assessment upon admission to ensure of diagnosis and inclusion criteria
- At Day 1:
  - a baseline visit followed by a randomization procedure, initiation of first infusion,
  - a post-infusion evaluation at 3 hrs (+/-1hr) after the end of administration.
- At Day 2:
  - Initiation of second infusion (pending results of prior evaluation)
  - A post-infusion evaluation at 3 hrs (+/-1hr) after the end of second administration if a second administration takes place.
- At Day 3:
  - Initiation of third infusion (pending results of prior evaluation)
  - A post-infusion evaluation at 3 hrs (+/-1hr) after the end of third first administration if a third administration takes place.
- At day 4: a follow-up evaluation at 96 hrs (+/- 3 hrs), post beginning of first administration (primary end-point recording).
- At day 5: a follow-up evaluation at 120 hrs (+/-3 hrs), post beginning of first administration.
- In case, the administration is not repeated, post-infusion evaluation at 3hrs at Day 2 and Day 3, Day 4 (96 hrs), Day 5 (120 hrs) visits should take place anyway.
- A follow-up visit at Days 7 (+/-1 day), 14 (+/- 2 days) and 20 (+/-2 days),

- A 40-day (+/-3 days) post-treatment final evaluation, (End-Of- Study visit).

Additional follow-up visits, or phone calls may be required on a need basis notably in case of emerging or prolonged adverse events. Remote visits utilizing specific devices can be undertaken if it is not desirable that the patient, if discharged comes back to the institution.

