### **WHO COVID-19 Scale**

The WHO COVID-19 Scale is 9-point ordinal scale and will not be considered as an interval scale. A categorical analysis will be performed.

A descriptive analysis of each category (count and percentage) will be performed by treatment group at each assessment day. The distribution of outcomes on WHO COVID-19 Ordinal Scoring Scale will also be described via plots (e.g., stacked bar plots representing the proportion of subjects in each category, by treatment arm, over time).

The distribution of the 9-point ordinal scale at each post randomization time point will be compared between groups with a Cochran-Mantel Haenszel test using modified ridit scores (i.e. categorical counterpart of the Wilcoxon test) and stratified by baseline WHO COVID-19 status.

In addition, an analysis will be performed on the change from baseline to each time point which will be transformed into a categorized 3-point ordinal scale as follows: worsened, unchanged, and improved. A descriptive analysis of each category (count and percentage) will be performed by treatment group at each assessment day. The distribution of outcomes will also be described via plots (e.g., stacked bar plots representing the proportion of subjects in each category, by treatment arm, over time).

The analysis of the 3-point ordinal scale will be performed with the same approach proposed for the 9-point ordinal scale. The analysis of the binary endpoint will be performed using a Cochran-Mantel Haenszel test (using modified ridit scores) stratified by baseline WHO COVID-19 status.

Missing data will be replaced by the last available value.

Subgroup analyses:

If feasible (i.e. when subgroup sizes are sufficient), analyses of the WHO COVID-19 scale will be performed by BMI (  $<30$  vs  $\geq 30$  ), Age (  $< 65$  vs  $\geq 65$  ), by baseline WHO-Covid-19 scale, comorbidity, concomitant medications with the same approach proposed for the FAS.

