**NEWS-2 scale**

NEWS2 is the latest version of the National Early Warning Score (NEWS) updated in December 2017. As the news-2 scale is not an interval scale, a categorical ordinal analysis will be performed. Thresholds on the aggregated score suggested by the Royal College of Physicians will be used to transform the NEWS-2 scale into a categorized scale (called hereafter the “categorized news-2 scale”). Further details on the thresholds will be provided in the SAP.

Missing values of the NEWS-2 scale not due to death will be replaced by the last available news-2 scale value before deriving the category of the categorized NEWS-2 scale. Missing values of the NEWS-2 scale due to death occurring prior to or on day D4 will be imputed in the highest category.

A descriptive analysis of each category (count and percentage) will be performed by treatment group at day D4.

The distribution of the categorized news-2 scale at Day D4 will be compared between groups with a Cochran-Mantel Haenszel test using modified ridit scores (i.e. categorical counterpart of the Wilcoxon test) and stratified by baseline categorized news-2 scale values.

The same analysis will be proposed at other time points (Days 1, 2, 3, 14, 20 and 40).

The distribution of outcomes on the categorized news-2 scale will also be described via plots (e.g., stacked bar plots representing the proportion of subjects in each category, by treatment arm, over time).

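### Last-value replacement of missing WHO and NEWS-2 scores makes no exception for patients discharged alive, so a known outpatient with no late score can be counted at an in-hospital level

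*Protocol*

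**What the plan says.** Protocol section 11.5.1 fixes the handling of missing scores for two secondary scales.

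- NEWS-2: "Missing values of the NEWS-2 scale not due to death will be replaced by the last available news-2 scale value". The only other rule concerns early deaths: "Missing values of the NEWS-2 scale due to death occurring prior to or on day D4 will be imputed in the highest category".
- WHO COVID-19 scale: "Missing data will be replaced by the last available value", with no exception.

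Both scales are compared late. After Day 4, the NEWS-2 text adds: "The same analysis will be proposed at other time points (Days 1, 2, 3, 14, 20 and 40"). For the WHO scale, "The distribution of the 9-point ordinal scale at each post randomization time point will be compared between groups".

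Follow-up after discharge may be remote. The Synopsis (Study design) says that "distant consultations by telemedicine may be undertaken if it is not deemed desirable that the patient comes back to the institution". Section 4.1 says "Should a patient being discharged before Day 40, a distant consultation should be undertaken", again on condition that a return to the institution is not desirable. Section 4.2 adds: "Remote visits utilizing specific devices can be undertaken if it is not desirable that the patient, if discharged comes back to the institution".

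The flowchart (section 7.1) and visit lists (sections 7.4 to 7.12) place the scales at the evaluations on Days 1 to 4 and on Days 7, 14, 20 and 40. No score is scheduled at discharge. The visit lists join the two scales with and/or, so a site that records only one of them has still followed the list.

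**The concern.** Among patients discharged alive, a late score can be missing because the patient was well enough to leave. The last recorded value then comes from the hospital stay and tends to be worse than the patient's condition at the visit. Last-value replacement is least suitable when leaving observation is itself the good outcome.

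For the WHO scale the value can contradict the trial's own data. In Appendix 2, scores 3 to 7 are the hospitalised categories, while a living patient out of hospital belongs at 0 to 2. A carried-forward 4 records a known outpatient as an inpatient on oxygen.

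What is at stake is the late comparison on two secondary scales. An arm that discharges more patients has more patients exposed to the error, which pulls the arms together. That matters because section 11.4 gives the trial's aim as estimating the treatment difference to help design later trials.

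**Working it through.** The plan states no figure on this point, so there is none to reproduce. I applied the rule to single records and then looked at its effect on a comparison.

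**NEWS-2 record, Appendix 1.** Day 7 in hospital: respiratory rate 22 (2 points), SpO2 94% (1 point), supplemental oxygen (2 points), other items normal (0 points). Total 2 + 1 + 2 = 5. The patient goes home on Day 10 and no NEWS-2 is recorded afterwards. The rule gives 5 at Days 14, 20 and 40, whatever the patient's condition.

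**WHO record, Appendix 2.** Day 7: hospitalised with oxygen by mask or prongs, score 4. The patient goes home on Day 10 and is not rescored. The rule gives 4 at Days 14, 20 and 40; the true score for a living outpatient is at most 2.

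If any score was recorded after discharge, that score is the one carried forward. The error therefore concerns patients with no score between discharge and the visit analysed.

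**Effect on a comparison.** The protocol gives neither discharge rates nor rates of missing scores, so both are assumed. Let d be the true proportion out of hospital at a late visit, and m the share of those patients with no score since discharge. Each of them is carried at WHO 3 or above.

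- Observed proportion out of hospital = d × (1 − m).
- With equal m in both arms, observed difference = (d₁ − d₂) × (1 − m).
- Power = Φ(|difference| ÷ √[(p₁(1 − p₁) + p₂(1 − p₂)) ÷ 30] − 1.96), where p is the observed proportion. This uses 30 per arm, one-sided alpha 0.025 and the unpooled Z test named in section 11.4. The planned test is a stratified Cochran-Mantel-Haenszel test on the full scale, so these powers are only illustrative.

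| Share unscored, m | Difference, 80% v 55% | Power | Difference, 90% v 70% | Power |
|---|---|---|---|---|
| 0 | 25.0 points | 57% | 20.0 points | 52% |
| 10% | 22.5 | 45% | 18.0 | 35% |
| 25% | 18.8 | 32% | 15.0 | 22% |
| 50% | 12.5 | 18% | 10.0 | 12% |

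The direction is unchanged when m is equal. With unequal m, for example 50% v 25% in the 80% v 55% case, the difference is 0.80 × 0.50 − 0.55 × 0.75 = 0.400 − 0.4125 = −1.3 points.

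**How many NEWS-2 records?** Assume that 50–90% are discharged before the visit, that 25–75% of those have no NEWS-2 since discharge, and that 40–60% of those have a last in-hospital score above the lowest category.

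- Low: 0.50 × 0.25 × 0.40 = 5% (3 of 60).
- Midpoints: 0.70 × 0.50 × 0.50 = 17.5% (10 to 11 of 60).
- High: 0.90 × 0.75 × 0.60 = 40.5% (about 24 of 60).

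If the second factor is zero, the result is zero. The third factor cannot be checked, because the NEWS-2 thresholds are left to the SAP.

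**The case against.** The strongest reply is that the protocol plans for these scores to exist. Days 14, 20 and 40 list the scales together with respiratory rate, SpO2, blood pressure, pulse and clinical evaluation, as well as ECG and local bloods, which suggest attendance in person. Remote contact is conditional, and devices are foreseen for it. With the scores recorded, the rule has nothing to replace. This stands: the error is conditional.

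The WHO part is the weaker one. Scores 0 to 2 need little more than infection status and activity limitation, which a telephone contact can supply, so the rule bites only if the site records nothing. For NEWS-2, which needs six physiological measurements, the risk is more real: nothing requires the devices to supply all six, and the and/or wording lets NEWS-2 be left out. Even so, some last in-hospital scores will already be low.

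A reader might infer that recovered patients generally stay scored as ill at the late visits, or that a true benefit would be pushed past the null. The documents support neither. The first needs late scores to be missing, at a rate the protocol does not give. The second needs missingness that differs by arm, and nothing in this double-blind protocol gives a reason to expect that beyond the difference in discharge itself.

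It is also fair that these are late time points of secondary endpoints in an exploratory trial. Discharge and recovery are measured directly by hospital-free days, oxygen-free days, clinical recovery and cure (section 9.1), and section 11.1 leaves further missing-data detail to the SAP. That lowers the weight of the point but does not remove it. The last-value rule is already fixed in the protocol, and as written it gives a wrong value for a known outpatient.

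**Conclusion.** The point holds in a limited form and is a cheap improvement. If a discharged patient has no score since discharge, the stated rule can carry a Day 7 or Day 4 in-hospital score to Days 14, 20 and 40 and record a known outpatient as still ill. This can happen chiefly for NEWS-2. With equal missingness in both arms it shrinks a true late difference in out-of-hospital status by the factor 1 − m and keeps its direction.

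The size is unknown. It runs from nothing, if all late scores are recorded, to the reductions shown above, all of which rest on assumed discharge and missingness rates. The primary endpoint is not affected: it is assessed at Day 4 and has its own missing-data rule.

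A separate gap lies in the same paragraph. NEWS-2 values missing because of death after Day 4 fall under neither stated rule, although later days are analysed. The conclusion here does not depend on it.

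**What to change.** In section 11.5.1, or in the SAP with the change recorded before unblinding:

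- Restrict last-value replacement for both scales to patients who are in hospital at the visit.
- For a patient known to be discharged alive, not readmitted and with no score at the visit, set the WHO score to 2, the worst ambulatory category.
- For the same patient, set the categorized NEWS-2 to its lowest category. If home oxygen is documented, count the 2 supplemental-oxygen points from Appendix 1 before assigning the category.
- Keep last-value replacement for all missing scores as a sensitivity analysis, and report how many scores were imputed by each rule, by arm and visit.

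The cost is a few lines of text. Hospital-free days already need discharge data; readmission and home oxygen at the visit must also be identifiable. The downside is that some discharged patients may be scored slightly too well. The sensitivity analysis errs in the other direction, so the two results together show how much the choice matters.

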#### **7.7 DAY-4 EVALUATION (96 hrs)**

Day 4, is the Day where the Primary efficacy endpoint is recorded

The following examinations will be performed:

- Clinical evaluation;
- 12-lead ECG;
- Respiratory distress parameters:
  - Respiratory Rate (RR),
  - Oxygen saturation (SpO2),
  - PaO2/FiO2;
- NEWS-2 and/or WHO scales;
- Optional Chest CT-scan;
- Local blood sample test;
- Soluble GPVI;
- Concomitant medication;
- Recording of adverse events according to NCI-CTCAE.

For the 4-day evaluation, a window of  $\pm 1$  hr is allowed.

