### 11.1 General considerations

In general, summary tabulations will be presented by treatment arm and will display the number of observations, mean, standard deviation, median, minimum, and maximum for continuous variables, and the number and percent per category for categorical data. The Kaplan-Meier survival curves and 25th, 50th (median), and 75th percentiles will be provided along with their 2-sided 95% confidence intervals (CIs) for time-to-event data.

The nominal one-sided alpha level of significance considered for statistical tests will be 0.025.

As this is essentially an estimation study, no adjustment for multiplicity will be proposed.

Methods for handling missing data will be further detailed in the SAP.

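### The NEWS-2 death rule stops at Day 4 while the same test is repeated to Day 40, so read literally the Day 14, 20 and 40 comparisons are survivors-only

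*Protocol*

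**What the plan says.** Protocol section 11.5.1, NEWS-2 scale, gives two imputation rules and then extends the analysis to other days.

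- Missing for reasons other than death: "Missing values of the NEWS-2 scale not due to death will be replaced by the last available news-2 scale value".
- Missing because of death: "Missing values of the NEWS-2 scale due to death occurring prior to or on day D4 will be imputed in the highest category".
- Repeats: after describing the Day 4 CMH test with modified ridit scores, it adds "The same analysis will be proposed at other time points (Days 1, 2, 3, 14, 20 and 40").

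The only item that this subsection leaves to the SAP is the category thresholds. Section 11.1 adds in general terms: "Methods for handling missing data will be further detailed in the SAP".

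The WHO subsection of 11.5.1 has one imputation sentence, "Missing data will be replaced by the last available value", and states that "The WHO COVID-19 Scale is 9-point ordinal scale and will not be considered as an interval scale". Appendix 2 lists death as a value of that scale, score 8.

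On data collection, most visit lists in section 7, including Day 4 in section 7.7, ask for "NEWS-2 and/or WHO scales". The flowchart in section 7.1 joins the two scales with an ampersand. Neither section 7.7 nor the flowchart's vital-signs row lists vital signs at the 96-hour visit.

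**The concern.** The death rule names a fixed day, but the analysis that it feeds does not stay on that day. Patients who die after Day 4 are the worst outcomes at Days 14, 20 and 40, and the text gives them no NEWS-2 category. If they are left out, the remaining groups are selected by an event that may depend on treatment, so the comparison is no longer between randomized groups. It would carry no information about deaths after Day 4. It could also lean either way, for instance against a drug whose additional survivors are sicker than the rest.

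Section 11.4 says that the study exists to estimate effects for the design of later trials. A NEWS-2 result at Day 40 that silently excludes late deaths could mislead that work.

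**Working it through.** **1. Apply the two NEWS-2 rules by date of death.**

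| Death occurs | Last value carried forward? | Highest category? | NEWS-2 value at Days 14, 20, 40 |
|---|---|---|---|
| On or before Day 4 | No, missing because of death | Yes | Highest category |
| Day 5 to Day 40 | No, missing because of death | No, after Day 4 | None at visits after death |
| Alive, visit missed | Yes | Not applicable | Last value |

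Days 1, 2 and 3 are unaffected, because a value missing there through death always comes from a death by Day 4. Late deaths are dropped. They are not under-scored, because the carry-forward rule excludes them.

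**2. Inputs for the size.** Section 11.4 gives illustrative death rates of 0.40 v 0.10 and 0.30 v 0.04, and 2 × 30 patients. It states no time horizon for these rates; I take them as Day 40 rates.

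**3. Reproduce the plan's figure.** Section 11.4 claims at least 80% power at one-sided 0.025 with an unpooled Z test. Power = Φ(|p1 − p2| / √(p1q1/n + p2q2/n) − 1.96), with n = 30.

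- 0.40 v 0.10: 0.30 / √(0.24/30 + 0.09/30) = 0.30 / 0.1049 = 2.860; Φ(2.860 − 1.96) = 81.6%.
- 0.30 v 0.04: 0.26 / √(0.21/30 + 0.0384/30) = 0.26 / 0.0910 = 2.857; Φ(2.857 − 1.96) = 81.5%.

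Both reproduce, so the rates and 30 per arm are the right inputs.

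**4. Patients with no Day 40 value.** Expected number per arm = 30 × death rate × (1 − share of deaths by Day 4). The protocol gives no such share, so a range is shown.

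| Share of deaths by Day 4 (assumed) | 0.40 v 0.10 | 0.30 v 0.04 |
|---|---|---|
| 0% | 12 v 3 | 9 v 1.2 |
| 10% | 10.8 v 2.7 | 8.1 v 1.1 |
| 30% | 8.4 v 2.1 | 6.3 v 0.8 |

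At 0%, 18 v 27 patients remain in the first scenario and 21 v about 29 in the second.

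**5. Illustration of what dropping them does to the test.** This was a simulation of an unstratified rank (ridit) test at one-sided 0.025, with 30 per arm and 3,000 runs. It used four NEWS-2 categories, survivors split 70/15/10/5% in both arms, and 0 to 30% of deaths by Day 4. None of the categories, the survivor split or the timing of deaths comes from the protocol.

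| Scenario | All deaths by the visit ranked worst | Deaths after Day 4 dropped |
|---|---|---|
| 0.40 v 0.10 | 56 to 57% | 3 to 16% |
| 0.30 v 0.04 | 46 to 47% | 3 to 10% |

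With survivors split 50/25/15/10% and all deaths after Day 4, the figures were 48% v 2.5% and 37% v 2.4%. The low end is the test's own alpha, because survivors were given the same distribution in both arms. The table shows direction only and does not estimate a loss in this trial.

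**6. WHO scale.** Score 8 is death and the full 9-point scale is analysed, so a recorded death is an observed worst score. Carrying the last value forward from it gives 8. No loss follows.

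**The case against.** **The Day 4 wording may be meant to move with the visit.** The death rule, the description and the test are all written for Day 4, and the subsection then says that the same analysis applies elsewhere. A sensible programmer could move the cut-off with the visit, and the SAP, which is not at hand, may say so. This is a fair reading and may be the intended one. It does not remove the point. The sentence names Day 4 explicitly, this subsection defers only the thresholds to the SAP, and a SAP that copies the sentence copies the gap.

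**Deaths are captured elsewhere.** This stands. Section 11.5.1 analyses Day 40 mortality and overall survival. Section 9.1 gives respiratory rate, hypoxemia and SpO2 status an explicit death category, and the WHO scale scores death 8. A reader might infer that a drug that prevents death gets no credit, or that one that causes death goes unpenalised. At trial level the protocol does not support that.

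**The WHO imputation sentence has no death exception.** A reader might infer that the WHO analyses score the dead as alive. Appendix 2 contradicts this. A risk remains only if sites leave visits after death blank and the last score while alive is used to fill them.

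**The power figures are largely built in.** This also stands. They rest on equal survivor distributions, an invented category split, an unstratified test where the plan stratifies by baseline category, and death rates that section 11.4 offers only as a rough guide.

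**The collection points are small.** The flowchart already schedules both scales at Day 4, and scheduling NEWS-2 implies measuring its components. Nor does the either/or wording appear at every visit: the Day 5 and screening lists name neither scale.

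**Conclusion.** The point holds for NEWS-2 at Days 14, 20 and 40. As written, a death after Day 4 receives no value and the later comparisons are restricted to survivors. At the protocol's illustrative rates this removes up to about 12 v 3, or 9 v 1, of 30 patients per arm at Day 40, and fewer if some deaths come early. That size assumes that the section 11.4 rates apply by Day 40 and that the sentence is followed literally.

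The Day 4 NEWS-2 analysis is not affected by this gap, nor are the WHO analysis of recorded deaths, the mortality and survival analyses, or the primary endpoint. The harm is limited to later repeats of one secondary scale in an exploratory study. It still merits correction, because the rule as stated gives a wrong result and the remedy is a single sentence. The differences in visit and scale wording are matters of alignment only.

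**What to change.** Replace the NEWS-2 death sentence in section 11.5.1 with: *for each time point, a patient who died on or before that time point is placed in the highest NEWS-2 category*. Carry the same wording into the SAP before unblinding. This costs one sentence and needs no new data, since dates of death are already required for overall survival.

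Minor alignments for the same amendment:

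- In the section 7 visit lists, replace the either/or wording so that both scales are required, as in the flowchart.
- In section 7.7 and the flowchart, list at Day 4 the vital signs that NEWS-2 needs (systolic blood pressure, pulse, temperature). This adds one routine set of measurements at one visit.
- In the WHO subsection, add a clause confirming that score 8 applies at every visit after death.
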